## Appendix C. Fear of Cancer Recurrence Inventory

Please read each statement and indicate to what degree it applied to you during the past month by circling the appropriate number.

**Table A3 brainsci-15-00900-t0A3:** Fear of Cancer Recurrence Inventory.

**0** **Never**	**1** **Rarely**	**2** **Sometimes**	**3** **Most of the Time**	**4** **All of the Time**				
The following situations make me think about the possibility of cancer recurrence:								
1. Television shows or newspaper articles about cancer or illness				0	1	2	3	4
2. An appointment with my doctor or other health professional				0	1	2	3	4
3. Medical examinations (e.g., annual check-up, blood tests, X-rays)				0	1	2	3	4
4. Conversations about cancer or illness in general				0	1	2	3	4
5. Seeing or hearing about someone who is ill				0	1	2	3	4
6. Going to a funeral or reading the obituary section of the paper				0	1	2	3	4
7. When I feel unwell physically or when I am sick				0	1	2	3	4
8. Generally, I avoid situations or things that make me think about the possibility of cancer recurrence				0	1	2	3	4
**0** **Not at all**	**1** **A little**	**2** **Somewhat**	**3** **A lot**	**4** **A great deal**				
9. I am worried or anxious about the possibility of cancer recurrence				0	1	2	3	4
10. I am afraid of cancer recurrence				0	1	2	3	4
11. I believe it is normal to be worried or anxious about the possibility of cancer recurrence				0	1	2	3	4
12. When I think about the possibility of cancer recurrence, this triggers other unpleasant thoughts or images (such as death, suffering, the consequences for my family)				0	1	2	3	4
13. I believe that I am cured and that the cancer will not come back				0	1	2	3	4
14. In your opinion, are you at risk of having a cancer recurrence?								
0 Not at all	1 A little at risk	2 Somewhat at risk	3 A lot at risk	4 A great deal at risk				
15. How often do you think about the possibility of cancer recurrence?								
0 Never	1 A few times a month	2 A few times a week	3 A few times a day	4 Several times a day				
16. How much time per day do you spend thinking about the possibility of cancer recurrence								
0 I don’t think about it	1 A few seconds	2 A few minutes	3 A few hours	4 Several hours				
17. How long have you been thinking about the possibility of cancer recurrence?								
0 I don’t think about it	1 A few seconds	2 A few minutes	3 A few hours	4 Several hours				
**0** **Not at all**	**1** **A little**	**2** **Somewhat**	**3** **A lot**	**4** **A great deal**				
When I think about the possibility of cancer recurrence, I feel:								
18. Worry, fear or anxiety				0	1	2	3	4
19. Sadness, discouragement or disappointment				0	1	2	3	4
20. Frustration, anger or outrage				0	1	2	3	4
21. Helplessness or resignation				0	1	2	3	4
My thoughts or fears about the possibility of cancer recurrence disrupt:								
22. My social or leisure activities (e.g., outings, sports, travel)				0	1	2	3	4
23. My work or everyday activities				0	1	2	3	4
24. My relationships with my partner, my family, or those close to me				0	1	2	3	4
25. My ability to make future plans or set life goals				0	1	2	3	4
26. My state of mind or my mood				0	1	2	3	4
27. My quality of life in general				0	1	2	3	4
**0** **Not at all**	**1** **A little**	**2** **Somewhat**	**3** **A lot**	**4** **A great deal**				
28. I feel that I worry excessively about the possibility of cancer recurrence				0	1	2	3	4
29. Other people think that I worry excessively about the possibility of cancer recurrence				0	1	2	3	4
30. I think that I worry more about the possibility of cancer recurrence than other people who have been diagnosed with cancer				0	1	2	3	4
**0** **Never**	**1** **Rarely**	**2** **Sometimes**	**3** **Most of the time**	**4** **All of the time**				
When I think about the possibility of cancer recurrence, I use the following strategies to reassure myself:								
31. I call my doctor or other health professional?				0	1	2	3	4
32. I go to the hospital or clinic for an examination				0	1	2	3	4
33. I examine myself to see if I have any physical signs of cancer				0	1	2	3	4
34. I try to distract myself (e.g., do various activities, watch television, read, work)				0	1	2	3	4
35. I try not to think about it, to get the idea out of my mind				0	1	2	3	4
36. I pray, meditate or do relaxation				0	1	2	3	4
37. I try to convince myself that everything will be fine or I think positively				0	1	2	3	4
38. I talk to someone about it				0	1	2	3	4
39. I try to understand what is happening and deal with it				0	1	2	3	4
40. I try to find a solution				0	1	2	3	4
41. I try to replace this thought with a more pleasant one				0	1	2	3	4
42. I tell myself “Stop it”				0	1	2	3	4
Do you feel reassured when you use these strategies?				0	1	2	3	4

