### 2.5. Sample Size Calculation

The sample size calculation takes into account the principle of minimization for randomization, with participants randomized into either the iEFT group, iMMI group, or WLC group. In order to achieve at least 80% power to detect a between-group difference in mean FCRI at T1 of 10 points using an independent samples *t*-test at the two-sided 2.5% significance level (two experimental groups are compared against a single control), a total sample size of 444 patients (148 in each group) is needed, assuming a common standard deviation for FCRI in all groups of 27.9 points.

When taking into account baseline FCRI as a covariate in the regression model, the calculated sample size can be reduced by a design factor equal to (1 – r^2^) [28]. Assuming a correlation between baseline and follow-up FCRI of 0.6, the sample size reduces to 288 patients in total. This sample size has been increased to 339 patients in total to allow for an expected drop-out rate of 15%. This means we will include 113 patients in each group: iEFT (intervention), iMMI (active control), and the WLC group.

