### 2.9. Analysis Plan

Primary outcome measures:The difference in mean scores from the baseline on the FCRI between the iEFT group and the WLC group at T1;The difference in mean scores from the baseline on the FCRI between the iMMI group and the WLC group at T1;

Secondary outcomes measures:Changes in emotional distress, QoL, and health status;The difference in mean scores from the baseline on the FCRI between the iMMI group and the WLC group;

Tertiary outcomes measures:Changes in the cortisol biomarker

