**Figure 2 brainsci-15-00900-f002:**
[figure not shown]
Head, torso, and hand acupressure points involved in the application of EFT (Figure adapted from Church et al. [29]). The process starts with a ‘Setup Statement’ while performing acupoint tapping on the side of the hand. For the remainder of the process, patients gently tap with two fingers on head and torso points while repeating the ‘Reminder Phrase’.

**Table 1 brainsci-15-00900-t001:** Secondary and tertiary objectives.

Secondary objectives
• Explore whether iEFT is more effective than iMMI for improving FCR
• Compare the efficacy of the two interventions relative to a WLC group on distress, QoL and health status
• Explore whether iEFT is more effective than iMMI (active control condition) for improving distress, QoL and health status
• Prevalence and predictors of FCR in cancer survivors
• The magnitude of the interventions to reduce FCR in cancer survivors
• The level of preference of the WLC group to (optionally) complete a course of iEFT or iMMI
• The level of efficacy of both interventions between younger and older cancer survivors (< or ≥50 years)
• The level of the efficacy of both interventions between cancer survivors participating within 1 year after ending curative therapy and cancer survivors participating ≥1 year after ending curative therapy
• The time spent by iEFT and iMMI practitioners (time toxicity per patient)
Tertiary objective *
• The effect of iEFT and iMMI on chronic biological stress measured as hair cortisol concentration.

* This objective will only be completed when the primary objective is positive.

**Table 2 brainsci-15-00900-t002:** Inclusion and exclusion criteria.

Inclusion criteria
• Minimum age of 18 years at the time of enrolment
• Dutch as main language
• Histologically confirmed diagnosis of a solid cancer or haematological malignancy
• Curative surgery, chemotherapy, radiation therapy, immunotherapy, hormone therapy, targeted drug therapy or a combination of these was completed at least 2 months ago and no longer than 5 years ago at the time of enrolment. *
• Expected life expectancy of at least 5 years
• Disease-free at the time of enrolment, as defined by the absence of somatic disease activity parameters
• High FCR based on the Cancer Worry Scale 6-item version [26] (cut-off ≥ 10)
• Sufficient mental and physical functional status
Exclusion criteria
• Treatment with palliative intent
• Mental deterioration

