**Medical data ^2^**				
**PROMs ^3^**				
Fear of Cancer Recurrence Inventory ^4^	X	X	X	X
Distress thermometer	X	X	X	X
38-item Problem List	X	X	X	X
EORTC QLQ-SURV100 ^5^	X	X	X	X
EuroQol EQ-5D-5L	X	X	X	X
**Biomarker cortisol** *	X	X		

Abbreviations: PROMs: Patient Reported Outcomes Measures; EORTC: European Organisation for Research and Treatment of Cancer; QLQ: Quality of Life Questionnaire; SURV100: survivorship questionnaire with 100 items; EuroQol: European Quality of Life. ^1^ T0: baseline (i.e., before randomisation); T1: 6 weeks after start of the iEFT or iMMI programme or 6 weeks after randomisation to the wait-list; T2: 6 weeks after end of the iEFT or iMMI programme or 12 weeks after randomisation to the wait-list; T3: 24 weeks after start of the iEFT or iMMI programme or 24 weeks after randomisation to the wait-list. ^2^ Details can be found in Supplementary Materials Section SC. ^3^ Details can be found in Supplementary Materials Section SD. ^4^ Details can be found in Appendix C. ^5^ Additionally, item 13, 14, 15, 16 and 17 of the EORTC QLQ-C30 have been added. * Optional, needs to be indicated in the Informed Consent Form (ICF).

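### As printed in Appendix C, FCRI item 17 (how long the thoughts have gone on) carries item 16's time-per-day response options; check the deployed form and correct the table

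*Protocol article*

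**What the plan says.** The primary outcome in Section 2.9 is built on the FCRI. The first of its two contrasts is "The difference in mean scores from the baseline on the FCRI between the iEFT group and the WLC group at T1", and the second is the same for iMMI. Section 2.5 sizes the trial on a "between-group difference in mean FCRI at T1 of 10 points using an independent samples" t-test. For the instrument itself, footnote 4 to the FCRI row of Table 3 tells the reader "Details can be found in Appendix C".

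Appendix C (Table A3) prints the whole questionnaire. Its instruction asks respondents to "indicate to what degree it applied to you during the past month by circling the appropriate number". Item 16 reads "16. How much time per day do you spend thinking about the possibility of cancer recurrence" and item 17 reads "17. How long have you been thinking about the possibility of cancer recurrence". Both are followed by one and the same answer row: 0 for not thinking about it, then "1 A few seconds", then minutes, a few hours and, at the top, several hours.

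The article does not explain the repeated row, give other options for item 17, or exclude the item from scoring. It prints no FCRI scoring rule. Table 3 refers details of the patient-reported measures to Supplementary Section SD, which is not shown.

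**The concern.** Items 16 and 17 ask different things: how much of a day the thoughts take up, and for how long the person has had them. A scale that stops at several hours fits the first question but not the second. Table 2 admits people whose curative treatment ended between 2 months and 5 years ago, so a truthful answer to item 17 will often be months or years, and no such option exists. A respondent might leave the item blank, choose the top option or repeat the answer to item 16. The documents do not say which.

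If the deployed questionnaire has the same row, one item of the primary outcome measure does not record what it asks. Checking early is worthwhile: Section 3 reports 82 of 339 participants on 31 July 2025, and Section 6 projects recruitment to March 2027.

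**Working it through.** **1. Is the mismatch in the document, or is it a text-extraction fault?** Items 14 to 17 of Table A3 each have their own answer row directly below the stem:

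| Item | What it asks | Answer row | Fits? |
|---|---|---|---|
| 14 | perceived risk | graded degree of risk | yes |
| 15 | frequency of thoughts | never, up to several times a day | yes |
| 16 | time per day | none, seconds, minutes, hours | yes |
| 17 | how long the thoughts have gone on | identical to item 16 | no |

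Row 17 is complete and in the right position. Only its content is wrong for the stem. This looks like a copying error in the table and not like a broken row.

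**2. Share of the score.** Assume that the total is the plain sum of the 42 numbered items, each scored 0 to 4. The maximum is then 42 × 4 = 168. Item 17 contributes at most 4 points, and 4/168 = 2.4%.

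**3. The plan's own sample size (Section 2.5).** Inputs: difference 10, SD 27.9, two-sided 2.5% level, 80% power, correlation 0.6, drop-out 15%.

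- Normal approximation: n per arm = 2 × (27.9/10)² × (2.241 + 0.842)² ≈ 148, total 444, as stated.
- The t-based version gives 150 per arm, total 450. The factor is 1 − 0.6² = 0.64, and 450 × 0.64 = 288, as stated. (Starting from 444, the product is 284.)
- 288/0.85 = 338.8, rounded up to 339, as stated.

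The sample size reproduces and does not depend on this point.

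**4. Illustration of the cost if the form is affected.** Suppose item 17 would have carried an equal 1/42 share of the 10-point effect and that share is lost entirely: 10 × 41/42 = 9.76. With 288/3 = 96 analysed per arm and adjusted SD 27.9 × √0.64 = 22.3:

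- standard error = 22.3 × √(2/96) = 3.22
- power at 10 points = Φ(10/3.22 − 2.241) ≈ 80.6%
- power at 9.76 points = Φ(9.76/3.22 − 2.241) ≈ 78.5%

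The loss is about 2 percentage points.

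**5. Direction.** All three arms complete the same questionnaire and allocation is 1:1:1 (Section 2.6). A fault that is constant throughout the trial affects the arms alike, so it gives no reason to expect bias in the contrast.

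**6. Room to act.** On 31 July 2025, 339 − 82 = 257 participants (76%) were still to enrol.

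**The case against.** The strongest reply is that Appendix C is probably not what participants see. It is in English and tells the reader to circle a number. Eligibility requires "Dutch as main language" (Table 2), and the Discussion refers to online questionnaires answered through MyNexuzHealth. The error may exist only in the article. This stands, and it makes everything beyond the misprint conditional.

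It can also be said that an affected item need not lose sensitivity. Respondents who repeat their item 16 answer turn item 17 into a second time-per-day item, which can respond to treatment, whereas a true time-since-onset item could hardly fall within six weeks. This also stands, and it is why the power figure is only an illustration.

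Three stronger readings are tempting, and the documents support none of them:

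- A reader might infer that the primary score is invalid as collected. The article shows neither the deployed form nor a scoring rule.
- A reader might set the item's 4 points against the 10-point target. The first is the largest possible shift in one person's item score, the second a difference between group means, so the two are not comparable.
- A reader might infer that the planning SD of 27.9 belongs to a different version of the instrument. Section 2.5 does not say where that SD comes from.

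The reply does not remove the error itself. The article names Appendix C as its reference for the primary measure, and what is printed there is wrong. It is more than a detail left to a fuller document.

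**Conclusion.** The point holds as an error in the printed primary instrument: item 17 in Appendix C carries response options that cannot answer its question. Whether it reaches the data is unknown.

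If it does, and if the total is a plain sum of 42 items, the effect is confined to 2.4% of the score range and is common to all arms. The likely consequence is a small loss of validity and precision, about 2 points of power under the equal-share assumption. There is no ground for expecting bias between arms, provided the form does not change between a participant's assessments. The matter is minor in size, but it concerns the primary outcome and is cheap to settle.

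**What to change.** 1. Check the response options and the coding of item 17 in the deployed Dutch electronic form against the validated version of the instrument. Do this now, while most of the 339 are still to enrol.
2. Correct item 17 in Appendix C, whatever the check shows.
3. If the deployed form carries the error, specify before unblinding a sensitivity analysis of both primary contrasts with item 17 left out.
4. In that case also keep one version of the form within each participant from T0 onwards. Under Section 2.2, T1 is counted from the first session in the intervention arms but from T0 in the wait-list arm, so a switch on a calendar date could fall between T0 and T1 in different proportions across the arms.
5. If the form is corrected for new participants, record the version each person used and account for it in the analysis.

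The cost is one form check, one table correction and, if needed, one extra model run. Step 5 has a real downside: it puts two versions into one pooled score. Whether to correct the form mid-trial or keep it and rely on the analysis without item 17 is therefore a judgement for the trial team, to be documented before unblinding.
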